## 5.2 Treatment procedures used in this clinical trial

### 5.2.1 Usual care (common to both groups): physiotherapy and patient education

Usual care consists of physiotherapy and education, provided twice per week for 4 weeks, for a total of 8 sessions.

#### (1) Physiotherapy (Interferential Current Therapy, ICT)

- Two pairs of electrodes (four pads) are attached in a crossed pattern centered on the area where pain is most severe, so that the interferential current focuses on the painful region.
- A medium-frequency alternating current of 4,000–4,100 Hz is applied for 15 minutes, and the intensity is adjusted according to the patient's subjective sensation so that pain is not felt.
- Treatment is administered twice per week for 4 weeks, for a total of 8 sessions.
- Devices used:
  - Catholic Kwandong University International St. Mary's Hospital, Department of Korean Medicine: STRATEC STT-570 (STRATEC Co., Ltd., Korea)
  - Wonkwang University Korean Medicine Hospital: EF-160 (OG Giken Co., Japan)

#### (2) Exercise guidance for patients

- At each visit, approximately 15 minutes of exercise instruction is provided, including: pelvic tilt exercises, trunk rotation without weight bearing, knee-to-chest exercises, partial curl-ups, and other exercises appropriate for low back pain.
- Patients are instructed in how to perform these exercises safely at home.

[figure not shown]

### (3) Patient education

- Educational materials and explanations are provided regarding postures that help prevent low back pain and appropriate working postures and ergonomics.
- Education focuses on modifying daily activities and occupational tasks to reduce mechanical stress on the lumbar spine.

[figure not shown]

### 5.2.2 Chuna manual therapy (applied only in the Chuna treatment group)

#### (1) Application of Chuna therapy according to radiograph–based diagnostic results

- In the Chuna treatment group, Chuna manual therapy is performed based on the Chuna diagnostic results derived from the plain radiographs.
- Treatment is provided twice per week for 4 weeks (approximately 15 minutes per session), for a total of 8 sessions.
- According to the diagnostic results, the standardized operating procedures (SOPs) specified in the protocol are used to select the treatment method.
- Based on the classification of Chuna diagnostic results into simple and complex malposition patterns, Chuna treatment methods specified in the SOP are applied to the corresponding vertebral levels.
- When more than one corrective technique is presented in the SOP for a given malposition, the practitioner may choose the most appropriate technique according to clinical judgement.
- If, in the clinical judgement of the practitioner, additional Chuna therapy is required for regions other than the lumbar spine (for example, the pelvis), such techniques may be applied, and these procedures will be recorded in the case report form.
- However, for the lumbar spine itself, no Chuna techniques other than those specified in the SOP may be applied.

#### (2) Determination of the exact treatment level using ultrasound prior to Chuna therapy

- To ensure accurate contact at the treatment level corresponding to the malposition identified on plain radiographs, ultrasound imaging is used to confirm the vertebral level before Chuna therapy.
- Using a longitudinal view, the shape of the spinous processes is visualized, and the levels are identified sequentially from S1 upwards.
- Once the target level is confirmed, the skin overlying the planned treatment site is marked.
- Chuna techniques are then performed at the marked level, following the standardized procedures described in the SOP.

[figure not shown][figure not shown]

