## 2) Blinding and unblinding

Due to the nature of the treatment interventions and study design in this clinical trial, it is not feasible to blind the clinical investigators and participants to group allocation. Instead, outcome assessors will remain blinded in order to minimize bias in the evaluation of participants. Because the clinical investigators and participants are not blinded, no specific unblinding procedure is planned.

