## 3) Outline of treatments in each group (summary)

- **Usual care (both groups)**
  - Interferential Current Therapy (ICT) applied to the painful lumbar region for **15 minutes per session**,
  - **Exercise guidance** (pelvic tilt, trunk rotation without weight bearing, knee-to-chest, partial curl-ups, etc.) for about **15 minutes** at each visit,
  - **Lifestyle education** and patient education materials on postures that help prevent low back pain and appropriate working postures.

→ Provided **twice per week for 4 weeks (total 8 sessions)** in both groups.
- **Chuna manual therapy (Group I only)**
  - In addition to usual care, standardized Chuna manual therapy is applied according to the **radiograph-based Chuna malposition diagnosis** confirmed at screening.
  - Techniques are selected according to the SOP for each malposition pattern (simple malposition, specialized techniques for simple malposition, simple techniques for complex malposition, specialized techniques for complex malposition).
  - Chuna therapy is provided **twice per week for 4 weeks (total 8 sessions, about 15 minutes per session)**.
  - Whenever necessary, ultrasound is used before treatment to confirm the exact vertebral level and mark the skin contact point.

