## 3) Treatment visits (Visits 3–10; both groups)

(1) Chuna + usual care group (Group I; Visits 3–10)

- Starting immediately after the baseline visit, participants receive treatment **twice per week for 4 weeks**, for a total of **8 sessions** according to the allocated intervention (usual care + Chuna).

(2) Usual care-only group (Group II; Visits 3–10)

- Starting immediately after the baseline visit, participants receive **usual care only** twice per week for 4 weeks (8 sessions).

(3) Assessments at each treatment visit (both groups)

- Before treatment at each visit, the following items are checked:
  - Occurrence of adverse events since the previous visit.
  - Vital signs: sitting blood pressure, pulse rate, body temperature (measured after at least 5 minutes in the sitting position without abrupt postural changes).

---

**4) Assessment visits** (same for Groups I and II – Visits 2, 10, and 11)

(1) All participants who pass screening will visit the outpatient clinic at baseline, at the end of the treatment period (4 weeks after baseline), and 8 weeks after completion of all treatments (12 weeks after baseline) to undergo the following assessments.

(2) Vital signs

(3) Assessment of subjective symptoms and function

- Primary and secondary efficacy outcomes are assessed using questionnaires on pain intensity and function: NRS, ODI, EQ-5D-5L, and RMDQ.

(4) Physical examination

- Lumbar range of motion (ROM):  
Flexion, extension, lateral flexion (right and left), rotation (right and left).

(5) Imaging evaluation

- Standardized lumbar spine AP and lateral standing radiographs (L-spine AP & lateral standing view) are obtained.
- Based on the acquired images, vertebral-level relative angles (flexion, extension, lateral bending, rotation) and Chuna malposition diagnosis results are derived using a DICOM labeling program and compared across time points.

(Note: No separate imaging assessment is performed at Visit 2; the imaging evaluation at Visit 2 is replaced by the screening radiographs obtained at Visit 1.)

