### 2. Physical examination – Lumbar range of motion (ROM)

- To evaluate changes in lumbar mobility, **lumbar ROM** is measured at baseline, week 4, and week 12, including:
  - Flexion,
  - Extension,
  - Lateral flexion (right and left),
  - Rotation (right and left).
- Measurements are performed using a standardized method (e.g., inclinometer or goniometer) according to the study site's SOP, and the degrees are recorded.

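### A skin mark made only in the Chuna arm is never removed or covered, so the blinded assessor may see it when measuring lumbar range of motion at week 4

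*Protocol*

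**What the plan says.** All references are to the protocol.

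- **Who is marked.** Section 5.2.2 is headed as applying to the Chuna group only. Its part (2) has ultrasound identify the vertebral level before treatment, and then: "Once the target level is confirmed, the skin overlying the planned treatment site is marked". Usual care (section 5.2.1) contains no marking.
- **How often.** Section 5.2.2 (2) reads as routine. The treatment outline in Section 7, part 3), says that "ultrasound is used before treatment to confirm the exact vertebral level and mark the skin contact point", but opens that sentence by limiting it to cases of need.
- **Schedule.** For Chuna: "Treatment is provided twice per week for 4 weeks (approximately 15 minutes per session), for a total of 8 sessions". Section 8, part 3), makes Visits 3 to 10 the treatment visits. Part 4) lists the assessment visits as "same for Groups I and II – Visits 2, 10, and 11".
- **Order within a visit.** Section 8, part 3), places only the adverse-event check and vital signs before treatment.
- **Blinding.** Section 7, part 2), says participants and investigators cannot be blinded, and that "outcome assessors will remain blinded in order to minimize bias in the evaluation of participants".
- **ROM.** Section 14.1 has lumbar flexion, extension, and left and right lateral flexion and rotation measured at baseline, week 4 and week 12, by inclinometer, goniometer or similar under a site procedure.

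**The concern.** Assessor blinding is the only masking in this trial, and the title announces it. It can do little for the pain scores and questionnaires, because participants rate these themselves and know their treatment. ROM is one of the few outcomes read by an examiner, so it is one where blinding can protect the comparison.

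The protocol creates a visible sign in one arm only, in the body region that the examiner measures, and says nothing about removing or hiding it. An examiner who sees the mark knows that the participant had Chuna. Even if only some Chuna participants are marked, every marked participant belongs to that arm. What is at stake is detection bias in the week-4 ROM comparison, arising while everyone follows the protocol as written.

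**Working it through.** The plan gives no figure on this point. The check is mainly a reading of the sections side by side, followed by one illustrative calculation.

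**1. Does a mark identify the arm?** Marking appears only under section 5.2.2 and in the Chuna part of the Section 7 outline. The usual-care sections have none. Yes, a mark identifies Chuna. The absence of a mark is less informative, because the Section 7 outline makes marking conditional.

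**2. Do marking and assessment fall on the same day?** Visits 3 to 10 are 10 − 3 + 1 = 8 treatment visits, so Visit 10 is session 8. Visit 10 is also the week-4 assessment. Yes.

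**3. How old is the latest mark when ROM is measured?** Eight sessions in 28 days is one every 28/8 = 3.5 days on average.

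| ROM measurement | Latest possible mark | Age of mark |
|---|---|---|
| Visit 10, after session 8 | session 8 | fresh |
| Visit 10, before session 8 | session 7 (Visit 9) | about 3 to 4 days |
| Visit 11 (week 12) | session 8 | about 8 weeks |

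The protocol permits both orders at Visit 10. In the first, any mark made that day is fresh. In the second, the assessor sees a mark only if it lasts 3 to 4 days, and the protocol gives neither its type nor its durability. At week 12 the route is remote.

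**4. Is the mark dealt with anywhere?** The sections on intervention, visits, blinding and ROM contain no removal, covering, matching mark in controls, or check of the back.

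**5. What could it do to a ROM comparison?** This step is illustrative.

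- *From the protocol:* 23 per arm, and two-sided α = 0.05. The 23 reproduces: 2 × (1.96 + 0.84)² / 0.96² = 17.01, rounded up to 18; then 18 / 0.8 = 22.5, rounded up to 23.
- *Assumed:* no true ROM difference, and an average shift δ (in SD units) in readings for the Chuna arm.
- *Formula:* the rejection probability of a two-sample t-test with 2n − 2 degrees of freedom and non-centrality δ√(n/2).

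| Assumed δ | Non-centrality, n = 23 | False-positive rate, n = 23 | False-positive rate, n = 18 |
|---|---|---|---|
| 0.2 SD | 0.68 | 10.2% | 9.0% |
| 0.3 SD | 1.02 | 16.9% | 14.1% |
| 0.5 SD | 1.70 | 38.2% | 30.8% |

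The n = 18 column is the plan's minimum after dropout. The shift δ is an average over the whole Chuna arm. If only half were marked and seen, a shift of 0.4 SD in those participants would average 0.5 × 0.4 = 0.2 SD, which is the first row.

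**The case against.** The strongest reply is that the protocol states nothing false here. It omits a small operational step that a site procedure might cover, in a 46-person pilot, for one secondary outcome at one time point. Several parts of that reply stand:

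- **Visibility is not established.** The protocol does not say that the back is bared for ROM, and the site procedure is not in the document. It also does not expressly say who takes the measurement. The assessor *may* see the mark; that they *will* is not shown.
- **Frequency is unsettled.** Section 5.2.2 (2) reads as routine and the Section 7 outline as conditional. All 23 Chuna participants being marked is an upper limit.
- **The error rates rest on assumptions.** No source in the protocol supports a shift of 0.2 to 0.5 SD, and ROM is not named among the outcomes listed for between-group testing in Section 15, part 2).

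A reader might also infer that the mark is a lasting ink mark, so that the assessor learns the arm whatever the order of procedures at Visit 10. The protocol does not support this. It does not mention ink, and if ROM precedes session 8, the inference needs a mark that survives 3 to 4 days.

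What does not stand is that the matter can be left to chance. Measuring ROM minutes after marking complies with the protocol as written, and nothing in it then protects the blinding that it promises.

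**Conclusion.** The point holds as a limited gap in the protection of assessor blinding. The protocol makes a skin mark in the Chuna arm only, combines session 8 with the week-4 assessment, leaves the order of ROM and treatment open, and never removes or covers the mark. The week-4 ROM assessor may therefore be unblinded: chiefly if ROM follows session 8, and otherwise only if a session 7 mark persists.

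The exposure is at most 23 of 23 Chuna participants against 0 of 23 controls, and it assumes that the lumbar skin is visible during measurement. The rates of about 10%, 17% and 38% show what a biased reading could do; they do not estimate what will happen here.

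A reader might infer that the trial's main result is compromised. It is not affected by this route: the primary NRS and the questionnaires are rated by participants who already know their arm, and week-12 ROM comes about 8 weeks after the last mark. The change is worth making because it is cheap and protects one of the few outcomes not rated by participants.

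**What to change.** 1. In section 5.2.2 (2) and in the Section 7 treatment outline, add: *The treating practitioner removes the skin mark completely at the end of each session, before the participant leaves the treatment room.*
2. In Section 8, part 4), add: *Before ROM is measured at Visit 10, treating staff who are not outcome assessors confirm that no mark is visible on the participant's back.* Covering the site identically in both arms before ROM is an alternative.
3. Reconcile section 5.2.2 (2) with the Section 7 outline on whether ultrasound and marking are routine or conditional.

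Fixing only the order at Visit 10 would not be enough, since a mark from session 7 might still be visible.

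**Cost.** One sentence in each place, seconds per session and no extra staff. The downside is that the level may have to be re-identified at the next session. Section 5.2.2 (2) already describes doing this before Chuna, but the Section 7 outline makes it conditional, so the extra work depends on how item 3 is settled.

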## ○ Lumbar Chuna techniques used in this trial

In this clinical trial, standardized lumbar Chuna manual therapy techniques are applied according to the radiograph-based Chuna diagnostic results.

The main lumbar techniques used in the study are as follows.

### ① Simple Chuna techniques for simple malposition

For patients in whom a **single simple malposition pattern** is identified (bilateral flexion, bilateral extension, rotation, or lateral bending), the corresponding “simple” lumbar Chuna technique is applied as the primary corrective procedure.

- **Bilateral flexion malposition – seated lumbar extension correction technique**
  - *Patient position:* Seated.
  - *Physician position:* Standing behind the patient.
  - *Contact and hand position:*
    - The treating hand (ju-dong-su) contacts the spinous process of the lower vertebral segment with the thenar/hypothenar region.
    - The other hand wraps around and holds the patient’s opposite shoulder and upper arm to fix the upper trunk.
  - *Corrective direction:*
    - With the upper body fixed, the physician extends the patient’s lumbar spine by guiding the trunk backward over the contact point on the lower segment, thereby correcting the bilateral flexion malposition into extension.
- **Bilateral extension malposition – seated lumbar flexion correction technique**
  - *Patient position:* Seated.
  - *Physician position:* Standing beside or slightly behind the patient.
  - *Contact and hand position:*
    - The treating hand contacts the spinous process of the lower segment.
    - The other hand supports the patient’s upper trunk and shoulders from the front.
  - *Corrective direction:*
    - The physician flexes the patient’s trunk forward over the contact point on the lower segment, applying a controlled flexion force to correct the bilateral extension malposition.
    - The patient is instructed to gently resist by attempting to straighten the trunk, while the physician applies counter-pressure, thereby performing an active-assisted correction.
- **Rotational malposition – side-lying lumbar traction technique with rotation**
  - *Patient position:* Side-lying, with the side of rotation directed downward.
  - *Physician position:* Standing in front of the patient, in a fencing-like stance.
  - *Contact and limb positioning:*
    - The lower leg is flexed, and the foot of the upper leg is placed in the

popliteal fossa of the lower leg.

- The caudal (foot-side) hand grasps the popliteal area of the upper leg, while the cranial (head-side) hand contacts the anterior aspect of the upper shoulder.

- *Corrective direction:*

- By simultaneously applying downward pressure through both hands, the physician produces rotational traction of the lumbar segment toward the corrective direction, thereby correcting the rotational malposition.

- **Lateral bending malposition – lumbar flexion–distraction technique with lateral bending**

- *Patient position:* Prone on a flexion–distraction (Cox) table. The feet are secured with a belt.

- *Physician position:* Standing at the side of the pelvic section of the table.

- *Contact and hand position:*

- The treating hand contacts the spinous process of the vertebral segment to be treated, using the thenar/hypothenar region.

- The other hand operates the handle of the Cox table.

- *Corrective direction:*

- While maintaining firm contact on the spinous process, the physician moves the pelvic section of the table to the left or right using the table handle, producing flexion–distraction combined with lateral bending at the target segment and correcting the lateral bending malposition.

## ② Specialized Chuna techniques for simple malposition

For patients with a **single simple malposition pattern** (bilateral flexion, bilateral extension, rotation, or lateral bending), more localized *segmental* techniques are used in addition to the simple techniques. These are applied when a stronger, more focused correction is required at a specific motion segment.

- **Bilateral flexion malposition – prone or side-lying lumbar extension thrust (spinous–process thrust technique)**

- *Patient position:* Prone or side-lying, with the target segment positioned near the edge of the table.

- *Physician position:* Standing in a fencing stance at the side of the table.

- *Contact:* The main (foot-side) hand uses the small thenar/pisiform region to contact the spinous process of the upper vertebra at the segment to be corrected. The assisting hand supports and stabilizes the patient's upper body or head.

- *Correction:* With the patient's trunk slightly flexed or neutral, the physician applies a quick, controlled downward and anterior thrust through the contact point to induce extension at the flexed segment and correct the bilateral flexion malposition.

- **Rotational malposition – prone “small–thenar–spinous/mammillary process” thrust technique**

- *Patient position:* Prone, with the head supported and the lumbar region centered on the table.
  - *Physician position:* Standing on the side opposite to the direction of rotation, in a fencing stance.
  - *Contact:*
    - For spinous–process contact: the small thenar/pisiform region of the main hand contacts the spinous process of the rotated vertebra.
    - For mammillary–process contact: the small thenar/pisiform region contacts the mammillary process on the side opposite to rotation.
  - *Correction:* The physician applies a short, high–velocity thrust in the direction opposite to the malposition (toward derotation), while stabilizing the trunk with the assisting hand. This “resisted thrust” technique is used when a more distinct rotational correction is needed.
  - **Lateral bending malposition – opened–wedge / closed–wedge mammillary–process thrust techniques**
    - *Patient position:* Side–lying on the flexion–distraction (Cox) or standard table, with the upper and lower legs positioned to create either an opened wedge or a closed wedge at the target segment.
    - *Physician position:* Standing in a fencing stance at the side of the pelvis.
    - *Contact:* The main hand uses the small thenar/pisiform region to contact the mammillary process of the target segment, while the assisting hand controls the patient’s shoulder or pelvis.
    - *Correction:*
      - **Opened–wedge approach:** The pelvic section of the table and the patient’s legs are positioned to open the wedge on the concave side, then a thrust is delivered toward the opened wedge to correct lateral bending.
      - **Closed–wedge approach:** The pelvic section and lower extremities are positioned to close the wedge on the convex side, and a thrust is delivered toward that side to restore balanced alignment.
- 

### ③ Simple Chuna techniques for complex malposition

For **complex malposition patterns** (e.g. extension + rotation + ipsilateral lateral bending; flexion + rotation + ipsilateral lateral bending; lateral bending with contralateral rotation), *simple multi–planar correction techniques* are applied first. These techniques combine flexion/extension, rotation, and lateral bending in a single maneuver, using leverage through the trunk and lower extremities.

- **Extension + rotation + ipsilateral lateral bending malposition – side–lying lumbar correction technique**

- *Patient position:* Side-lying with the involved side downward. The lower leg is extended, and the upper leg is placed over the lower leg or positioned to create slight lateral bending at the target segment.
- *Physician position:* Standing in front of the patient in a fencing stance.
- *Contact:* The physician's forearm (assisting arm) contacts the anterior shoulder of the patient, and the other hand or forearm controls the lower extremities (usually the ankle or distal leg of the lower limb).
- *Correction:*
  - The trunk is flexed to the level of the involved segment, and rotation is induced by pushing the shoulder backward while monitoring motion at the target level.
  - Simultaneously, the lower extremities are lifted upward to create lateral bending in the opposite direction, thereby correcting the combined extension-rotation-lateral bending pattern with a smooth, non-thrust mobilization.
- **Flexion + rotation + ipsilateral lateral bending malposition – side-lying lumbar correction technique**
  - *Patient position:* Side-lying with the involved side downward, similar to the above technique.
  - *Physician position:* Standing in a fencing stance.
  - *Contact:* As above, the assisting forearm stabilizes the shoulder, and the other hand controls the lower extremities.
  - *Correction:*
    - The trunk is extended from a flexed position while rotation is induced by the forearm on the shoulder.
    - The legs are elevated or lowered to generate corrective lateral bending, and the physician monitors motion at the target segment during the maneuver.
- **Lateral bending with contralateral rotation – seated or flexion-distraction-based correction**
  - *Patient position:* Seated or prone on a flexion-distraction table, depending on the segmental pattern.
  - *Physician position:* Standing behind or beside the patient.
  - *Contact:* One hand stabilizes the pelvis or lower trunk, while the other guides the thorax or shoulders.
  - *Correction:* The physician combines flexion or extension with rotation and opposite-side lateral bending of the trunk, using continuous mobilization rather than thrust, to reduce the complex pattern.

---

